## Introduction

1

Colorectal cancer (CRC) represents the third most common cancer and is the second-leading cause of cancer-related deaths worldwide (1, 2). The exact etiology of CRC remains unclear, although several studies have focused on the evaluation of the mechanisms involved. Most CRC cases (approximately 90%) occur sporadically (not related to the genetics of family with history of the disease), and several lifestyle factors including obesity, diet with a high content of fat and/or red and/or processed meat, environmental pollutants, cigarette smoking, and alcohol abuse, have been associated with CRC development and progression (2–4). Furthermore, there is emerging evidence that patients with CRC display significant alterations in gut microbiota, mainly characterized by an increase in opportunistic pathogens (e.g., *Enterococcaceae*, *Campylobacter*) (5, 6) and a decrease in butyrate-producing bacteria, including *Bifidobacteria*, *Roseburia* and *Faecalibacterium prausnitzii* (5–8). Overall, these alterations in the gut microbiome have been proposed to play an important role in tumor formation and progression (8–11).

As the initial genetic composition of all cells of a single human is identical, it is fairly questionable why the cells of the distal small bowel have 200 times reduced risk of cancer, when compared to the proximal large bowel (12–14). On the one hand, embryological development of human gastrointestinal tract through foregut, midgut and hindgut structures may play the most significant role. Whilst the right and proximal two-thirds of the transverse colon are midgut structures like the majority of the small intestine, the remaining distal colon and rectum are embryologically formed from the hindgut (15). Therefore, structurally, functionally and, in general, ontogenetically small and large intestines are different organs. Nevertheless, the role of continuous presence of microbes and decreasing immune cell infiltration towards distal large bowel cannot be diminished (16). Particularly, the composition of site-specific (luminal, and especially, mucosa-associated) bowel microbiota, along with the changes in local immune response have been discovered to have direct and indirect implications on anti- and procarcinogenic act in the gut (16–18).

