### Objectives and tasks of the study

1.2

The primary objective of the study is to identify the gut microbiota and immune infiltration patterns around normal bowel tissue, early adenoma, advanced adenoma, carcinoma *in situ* and invasive carcinoma.

The secondary objectives of MIMICA-1 are to investigate whether intestinal microbiota correlates with local immune response, and to compare mucosa-associated and fecal-derived microbiota compositional changes in healthy patients and along the adenoma-carcinoma sequence.

The aim will be achieved by performing the following tasks within the study:

To evaluate the normal microbiota of the distal small bowel, the right side of the large bowel and the left side of the large bowel and correlate the microbiota of the bowel wall to the stool microbiota;To determine the microbiota of the early (<1cm) adenoma, advanced (>1cm) adenoma, carcinoma *in situ* and invasive carcinoma and to compare it to the microbiota of the normal bowel as well as in the healthy segments of the small and large bowel;To study the normal immune infiltration (in the form of count, density and distribution of immunocompetent cells in epithelial and stromal tissue compartments) of the normal small and large bowel and to correlate it to the normal bowel wall and stool microbiota;To compare the normal immune infiltration to the immune infiltration around the early (<1cm) adenoma, advanced (>1cm) adenoma, carcinoma *in situ* and invasive carcinoma of the large bowel;To identify, whether changes in microbiota and immune environment interrelate and correlate with the progression of the dysplastic changes within the epithelium of the large bowel;To collect and contain colon mucosal biopsies in a biobank for further examination of intestinal epithelial cell oncogenic mutations and its correlation between gut microbiota’s compositional changes and the response of the intestinal immune system in the healthy small bowel and colon mucosa, and across adenoma-carcinoma sequence (in simple CR adenoma (< 1 cm); advanced CR adenoma (≥ 1 cm), Ca *in situ* and CRC).

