#### Questionnaires and physical evaluation

2.2.3

The personal information of the subjects will be conducted through the hospital’s indoor database and advanced health information questionnaires. Patients will be provided with questionnaires containing questions on demographics, anthropometric data (height, weight, body mass index (BMI) and waist circumference), health history, gastrointestinal disorders and interventional procedures, bowel symptoms, co-morbidities (including tobacco and alcohol consumption), use of certain medication (as antibiotics, probiotics, statins, proton pump inhibitors, corticoids and immunomodulators), dietary and ecological habits and possible microplastic intake. Physical evaluation will be assessed by the anesthesiologist on the procedure day.

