#### Sample size calculation

2.2.4

Since there is no clinical trial assessing the composition of intestinal microbiota; the count, density and distribution of immunocompetent cells in epithelial and stromal compartments, and the interrelations of both along every step of conventional adenoma-carcinoma pathway and healthy colon, endpoints of the study are currently unable to be determined. Thus, the sample size is estimated based on the data from a previous clinical trial (36), where 10 participants per group had 80% power at an alpha level of 0.05 and beta level of 0.2 to detect significant differences. The sample size in this study was calculated statistically by G*Power 3.1.9.4. Considering the expected withdrawal of participants during the intervention, we plan to recruit from 10 to 15 participants per group. This results in minimum 50 patients, 190 biopsy locations, 570 tissue samples, and a total number of 2280 specimens (staining using 4 antibodies) to be examined histologically and immunohistochemically. Plus 50 fecal and 570 tissue samples to be 16S rRNA sequenced (after DNA extraction) for precise analysis of gut microbiota structure. Overall, despite the inter-individual heterogeneity, with this sample size, differences in gut microbiota composition and local immunity changes are considered to be detectable.

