## Data and statistical analysis

4

The questionnaires and other measured data during the visit will be collected on paper and then transcribed to a secure electronic version on a locked office computer. The paper version of the data will be locked in a bookcase. Only the investigators running the study will have access to the final study dataset.

The obtained data will be analyzed by the SPSS software V26.0 (IBM, USA). The count, density, and distribution of immunocompetent cells (CD3, CD8, CD20, CD68) in epithelial and stromal compartments of adenoma, Ca in situ, CRC and the healthy controls will be performed. Here, continuous data with normal distribution will be expressed as mean ± standard deviation (SD), while data that is not normally distributed as median and range. Categorical data (especially from the questionnaires) will be expressed as the number of cases (n) and percentage (%). Kruskal-Wallis Test followed by Dunn’s Test will be employed for multiple pairwise comparisons of differences between two and more groups.

As for statistical analysis of microbial data, relative abundances, alpha and beta diversity will be performed. Principal Coordinates Analysis (PCoA) will be executed after calculating Bray-Curtis dissimilarity and UniFrac distances between samples. Beta diversity analyses will involve the application of Hellinger transformation to account for the compositional nature of microbiome data. Cluster analysis will be performed using Analysis of Similarities (ANOSIM) to assess the significant differences in microbial community composition between sample groups. Redundancy analysis will be used to identify factors that influence the structure of the microbiome. Alpha diversity will be calculated through the Shannon index, Simpson index, and Chao1 metrics after appropriate rarefaction. For the identification of differences in specific taxa between groups, ANCOM and LEfSe analysis will be conducted.

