In addition, the mentioned sampling of the normal-appearing intestinal tissue provides us with a self-control cohort of specimens from the same patient. This additional control group could prevent us from misleading interpretations while comparing gut microbiota composition among various dysplastic lesions, different colon sites, both intra- and interindividually.

Considering all this, MIMICA-1 is one of the pioneering studies to assess the interrelation of microbial, histologic, intestinal immune and oncogenic (in future study) changes in a multidisciplinary manner and in every step of conventional colorectal carcinogenesis. Our study also seeks to elucidate whether and how vast the difference is between fecal- and tissue-derived gut microbiota’s compositions in patients with colorectal neoplasia. As multiple trials show, the examination of mucosa-associated microbiota can provide more specific compositional information compared to stool samples representing luminal microbiota (6, 8, 32–35, 58). While fecal samples are less stable, depending on diet, BMI and behavioral factors, they are still easier to obtain, repeatable, and thus, more suitable for identification of noninvasive diagnostic and prognostic markers in CRC (59, 60). Similarly, this trial is expected to provide evidence for the benefits of more profound understanding of human intestinal microbiota studies, in general, and the role of appropriate sample matrix selection in future studies.

Moreover, the newly colon-site adapted AI-based digital image analysis of immune infiltrates is able to predict long-term outcomes of colon carcinoma (61, 62). Analyzing count, density, and spatial distribution of immunocompetent cells in epithelial and stromal tissue compartments of colorectal adenoma could also become an additional pathologic instrument to predict its further progression to CRC.

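### The stage comparisons the protocol names (Kruskal-Wallis/Dunn, ANOSIM) cannot adjust for the covariates it collects, so imbalance could appear as a stage effect in between-patient contrasts

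*Protocol article*

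**What the plan says.** Under Data and statistical analysis (section 4), counts, densities and distributions of CD3, CD8, CD20 and CD68 cells are compared by Kruskal-Wallis and then Dunn: "Test will be employed for multiple pairwise comparisons of differences between two and more groups". Differences in community composition between groups are tested by ANOSIM, and taxa by ANCOM and LEfSe. No covariate is attached to any of these. Categorical questionnaire data are to be summarised as counts and percentages. Redundancy analysis is planned to find factors that shape the microbiome; the factors are not named.

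The covariates will be in hand. Section 2.2.3 collects demographics, "anthropometric data (height, weight, body mass index (BMI) and waist circumference", tobacco and alcohol use, and dietary habits. The protocol treats several of them as relevant. The Introduction links colorectal cancer to "several lifestyle factors including obesity, diet with a high content of fat", as well as to smoking and alcohol. Section 5.1 says of stool: "While fecal samples are less stable, depending on diet, BMI and behavioral factors".

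The primary outcomes (section 3.1) are differences by location and by step of dysplasia, set against healthy controls. One task in section 1.2 asks whether the changes "correlate with the progression of the dysplastic changes within the epithelium of the large bowel". Section 3.1 lists correlation with dysplasia grade as a secondary outcome, with no method named.

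**The concern.** This is an observational cohort in which patients enter a stage group by diagnosis. Lesion patients come through screening, surveillance, symptoms and surgical lists, while the abstract and the control inclusion criteria take healthy patients from screening colonoscopy. Nothing describes matching. Age, BMI, diet or smoking may therefore differ between group V and the lesion groups, or along the sequence.

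A rank test of the five groups cannot separate such a difference from stage. If the covariate also affects the immune or microbial outcome, the omnibus test and Dunn's comparisons carry its effect and it would be read as part of carcinogenesis. The same holds for ANOSIM, which compares groups on distances alone. This bears on the primary outcome, because the comparison with healthy controls is a between-patient one.

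**Working it through.** **The plan's own figure.** Section 2.2.4 relies on an earlier trial in which "10 participants per group had 80% power at an alpha level of 0.05 and beta level of 0.2 to detect significant differences". This cannot be reproduced: no effect size, SD or test is given, and the section says that "endpoints of the study are currently unable to be determined". Back-solving a two-sided t test with 10 per group, alpha 0.05 and 80% power gives a standardised difference of 1.32. I use it only as a benchmark effect.

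**Inputs from the protocol.** Five groups of 10 (Table 2), so N = 50; threshold p < 0.05.

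**Inputs assumed.** One covariate X whose mean rises linearly by T SD from controls to cancer, with T = 0.5 to 2; within-group correlation r = 0.3 or 0.5 with the outcome; normal errors; no stage effect.

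**Formulas.**
- Spurious control-to-cancer difference = r × T, in outcome SD.
- Kruskal-Wallis: H = 12/(N(N+1)) × Σ(R_j²/n) − 3(N+1), referred to chi-square on 4 df. X enters nowhere.
- Adjusted group test: F = [(RSS0 − RSS1)/4] / [RSS1/(50 − 6)], where RSS0 is the residual sum of squares with X only and RSS1 with X and stage.

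**Result with no stage effect** (rejection rates by simulation, 10,000 runs per scenario in the check; simulation error about 1 point):

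| r | T | r × T | Kruskal-Wallis | Adjusted group F | Unadjusted trend test |
|---|---|---|---|---|---|
| 0.3 | 0.5 | 0.15 | 5% | 5% | 7% |
| 0.3 | 1.0 | 0.30 | 7% | 5% | 11% |
| 0.3 | 1.5 | 0.45 | 10% | 5% | 19% |
| 0.3 | 2.0 | 0.60 | 16% | 5% | 30% |
| 0.5 | 0.5 | 0.25 | 6% | 5% | 10% |
| 0.5 | 1.0 | 0.50 | 12% | 5% | 23% |
| 0.5 | 1.5 | 0.75 | 22% | 5% | 43% |
| 0.5 | 2.0 | 1.00 | 39% | 5% | 67% |

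The trend test is Jonckheere-Terpstra. It is more exposed than Kruskal-Wallis because the drift runs in the direction it looks for.

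**Cost of adjusting.** With a true linear rise of 1.325 SD and r = 0.3, power is 66% for Kruskal-Wallis and 74% for the adjusted group test when X is balanced. If X drifts by 1 SD, the adjusted group test falls to 68%.

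**Does stage order help?** Power with no covariate and a total effect of 1.325 SD:

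| Pattern across the five groups | Kruskal-Wallis | Jonckheere-Terpstra |
|---|---|---|
| Equal steps, control to cancer | 66% | 88% |
| One step (all lesions, or cancer only) | 77% | 63% |
| Peak at the middle stage | 72% | 3% |

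Ordering gains about 22 points (88 − 66) for a graded rise and loses about 14 (77 − 63) for a single step.

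**The case against.** The strongest objection is that covariate lists and adjusted models usually sit in a full protocol or analysis plan, and neither is shown. That would dispose of a complaint that covariates are merely unlisted. It does not dispose of this one: the article itself names the tests for the stage comparisons, and those tests cannot take covariates.

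The design also protects more than a reader might assume. Each lesion patient supplies normal ileum, right colon and left colon as self-controls (section 3.1.3.1), so patient-level factors cancel in lesion-versus-own-normal contrasts. The exclusion criteria remove recent antibiotics, long-term proton pump inhibitors, regular statins or probiotics, and steroids. Redundancy analysis can in principle condition on covariates, but as described it names no factors, is not tied to the stage comparison, and covers the microbiome only. These points narrow the concern to between-patient contrasts and to factors such as age, BMI, diet and smoking.

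A reader might go further and infer that an ordered test should be the primary analysis because the hypothesis speaks of progression. The documents do not support that. The primary objective is to identify patterns at each stage, which an omnibus test with pairwise follow-up addresses; correlation with dysplasia grade is already a secondary outcome; and section 5.1 expects cancer-stage communities to be secondary alterations, different in kind from adenoma patterns. The power tables show a trade-off, not a general loss.

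**Conclusion.** The concern holds for between-patient contrasts: each stage against group V, stage against stage, and stool. There, covariate imbalance could pass as a stage effect, and the named tests offer no means of removing it. Under the assumed drifts and correlations the false-positive rate runs from about 5%, which is no inflation, to about 39%, against about 5% when the covariate is in the model.

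The upper end needs a 2 SD drift and a correlation of 0.5. The documents give no covariate distribution by group, and they do not single out age as a confounder. So it would be wrong to say that age, diet or BMI differences will be reported as stage effects, or to quote only the upper figures. The simulation covers one normally distributed covariate with a linear drift, for an outcome of the immune or alpha-diversity kind. For ANOSIM the argument is structural, and no rate was computed.

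**What to change.** - **Immune and alpha-diversity outcomes, between patients.** Add a regression on patient-level values (log or rank scale) with stage as a factor, adjusted for a short prespecified set of collected covariates, for example age and BMI. Compare matching sampling sites. Leave out any lesion-side term when group V is included, since controls have no lesion.
- **Community composition.** Replace ANOSIM by PERMANOVA with the same covariates, and add a check of within-group dispersion.
- **Progression.** Add an adjusted ordered-stage term as a supplementary analysis. Do not rely on an unadjusted trend test.
- **Keep** Kruskal-Wallis and Dunn as the unadjusted description, and keep the lesion-versus-own-normal contrasts.

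The change is to analysis wording and needs no new data. With stage as a factor and two covariates, the model uses 1 + 4 + 2 = 7 parameters and leaves 50 − 7 = 43 residual degrees of freedom, against 45 without covariates. Power falls when covariates are strongly related to stage, which is why the set should be short. The trend term gains power only for a graded rise and loses it for single-step or non-monotone patterns, which is why it stays supplementary.

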### Data collection and management

3.1

Assessment of participants will be conducted at the pre-procedure (-t1), procedure (0) and post-procedure (t1-t4) timepoints. The detailed schedule of assessments is depicted in **Table 1**. The primary outcomes will be the differences in the microbiota composition and immune infiltration in different localizations of the tumor and different steps of mucosa dysplastic lesions compared to healthy controls. The secondary outcomes include correlation analysis of gut microbial diversity, intestinal immunity variables and the grade of colorectal dysplasia assessed for the study.

**Table 1 T1:** Study schedule of enrolment, interventions, and assessments.

	STUDY PERIOD						
	Enrolment	Allocation	Examination and analysis period				Close-out
TIMEPOINT	*-t_1_ *	0	*t_1_ *	*t_2_ *	*t_3_ *	*t_4_ *	*t_x_ *
ENROLMENT:							
Eligibility screen	X						
Informed consent + filling the questionnaire	X						
Allocation		X					
INTERVENTIONS:							
Collection of fecal samples	X	X					
Colonoscopy + endoscopic polypectomy (or biopsy) and normal gut tissue sampling or right hemicolectomy and gut tissue sampling	X		X				
ASSESSMENTS AND DATA ANALYSIS:							
Pathologic investigations: HE and IHC	X	X	X				
16S rRNA gut tissue- and fecal-derived microbiota sequencing			X	X	X	X	
AI-based digital image analysis			X	X	X	X	
Qualitative data analysis based on the questionnaires		X	X				
Data analysis on intestinal immune infiltration variables: count, density, and distribution of CD3, CD8, CD20, CD68 cells in epithelial and stromal compartments				X	X	X	X
Data analysis on gut microbiota compositional changes in tissue and stool samples: relative abundance, α- and β-diversity, etc.				X	X	X	X
Correlation analysis of gut microbiota and immune response variables in different site of the colon along the adenoma-carcinoma sequence						X	X

X, mark the appropriate period for the enrollment, interventions and other activities during the project

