The correlation between the gut bacterial composition and intestinal immune system response in adenoma-carcinoma sequence, and the healthy patients will be examined. Furthermore, fecal samples will be explored for gut microbiota alterations, comparing fecal- and tissue-derived bacterial compositions in healthy gut and along the steps of conventional colorectal carcinogenesis. The results will be regarded as statistically significant if p values < 0.05. In case of a relevant number of missing values, multiple imputation or pattern mixture models will be used.

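### ANOSIM, the only named between-group test of whole-community composition, cannot separate a compositional shift from a difference in spread, and can err in either direction

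*Protocol article*

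**What the plan says.** All of the following is in the protocol article.

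- Data collection and management makes composition a primary outcome, alongside immune infiltration: "The primary outcomes will be the differences in the microbiota composition and immune infiltration in different localizations of the tumor", and across the stages of dysplasia compared with healthy controls.
- Data and statistical analysis sets the distances ("Principal Coordinates Analysis (PCoA) will be executed after calculating Bray-Curtis dissimilarity and UniFrac distances between samples") and a transformation ("Beta diversity analyses will involve the application of Hellinger transformation to account for the compositional nature of microbiome data").
- The between-group test follows: "Cluster analysis will be performed using Analysis of Similarities (ANOSIM) to assess the significant differences in microbial community composition between sample groups".
- Two other inferential tools have other roles. For explanatory factors: "Redundancy analysis will be used to identify factors that influence the structure of the microbiome". For single taxa: "For the identification of differences in specific taxa between groups, ANCOM and LEfSe analysis will be conducted". Alpha diversity is summarised separately by the Shannon, Simpson and Chao1 measures.
- The threshold is common to all: "The results will be regarded as statistically significant if p values < 0.05".
- Sample size calculation plans 10 to 15 participants per group, so group sizes need not be equal. Limitations of the study adds that, if carcinoma in situ recruits poorly, it may be combined with adenocarcinoma, which could also unbalance the groups.

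**The concern.** ANOSIM asks whether ranked distances between groups exceed ranked distances within groups. Two groups with the same centre but different spread can meet that description, so a significant result may mean that the typical community differs or that one stage varies more from patient to patient. These are different biological statements. The article's hypotheses concern the first: characteristic bacterial patterns at each stage.

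Unequal spread is possible here. Table 2 restricts Group I to low-grade dysplasia but lets Group II mix low and high grade. Lesions under 1 cm are sampled beside the lesion and the others in it. The article acknowledges heterogeneity between individuals but does not quantify it. A significant ANOSIM could therefore be reported as a shift along the adenoma-carcinoma sequence when only variability changed. In other configurations a real shift could be missed.

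**Working it through.** **The plan's own figure.** The article gives no error rate or power for ANOSIM. Its only design figure, from an earlier trial, is: "10 participants per group had 80% power at an alpha level of 0.05 and beta level of 0.2 to detect significant differences". No effect size, SD or test accompanies it, so it cannot be reproduced and does not bear on how ANOSIM behaves.

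**Inputs.** From the article: 10 to 15 per group, five groups, alpha 0.05. Assumed, because the article gives none: the ratio k of the SD in the more variable group to that in the less variable one, shown from 1 to 1.5. Data are normal in q = 30 dimensions with identical centres and Euclidean distance, one sample per patient.

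**Statistics.**

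- ANOSIM: R = (mean between-group rank − mean within-group rank) / (N/2), where N is the number of pairwise distances.
- PERMANOVA: F = [(SST − SSW)/(g − 1)] / [SSW/(n − g)], where g is the number of groups, n the total number of samples, SST = sum of all squared distances / n, and SSW = the sum over groups of squared within-group distances / group size.

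**Why the direction depends on group size.** In units of q × variance, the expected squared distance is 2 within the tighter group, 2k² within the looser group and 1 + k² between them. At k = 1.25 these are 2, 3.125 and 2.5625.

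- 15 tight v 10 loose: 105 tight and 45 loose within-group pairs. Mean within = (105 × 2 + 45 × 3.125)/150 = 2.3375, below 2.5625. R is pushed up.
- 10 tight v 15 loose: 45 and 105 pairs. Mean within = (45 × 2 + 105 × 3.125)/150 = 2.7875, above 2.5625. R is pushed down.
- 10 v 10: 45 and 45 pairs. Mean within = 2.5625, equal to the between value. Squared distances balance, which is why PERMANOVA holds its level here. Ranks do not balance: mean R is about 0.04 at k = 1.25 and 0.09 at k = 1.5.

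**Rejection rates at 0.05** (2000 simulated data sets per row, 499 permutations; the less variable group is listed first):

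| Sizes | SD ratio | ANOSIM | PERMANOVA |
|---|---|---|---|
| 10 v 10 | 1 | about 5% | about 5% |
| 10 v 10 | 1.1 | 6–7% | about 5% |
| 10 v 10 | 1.25 | 18% | about 5% |
| 10 v 10 | 1.5 | 61% | about 5% |
| 15 v 10 | 1.25 | over 90% | about 11% |
| 10 v 15 | 1.25 | about 0% | 1–2% |
| 15 v 10 | 1.5 | about 100% | 17% |
| 10 v 15 | 1.5 | about 0% | 1% |

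**Five groups of 10** (600 data sets). With SD rising in equal steps from 1.0 to 1.5, ANOSIM rejects in about 38% and PERMANOVA in about 5–6%. With one control group and four equally more variable groups, ANOSIM is at or below 5%. The pattern of spread matters as well as its size.

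**Bray-Curtis check** (Dirichlet-multinomial, 50 taxa, same mean composition; lower precision means more spread). For 10 v 10 with precision 50 v 35, 25 and 12.5, ANOSIM rejects in 9.0%, 30.0% and 97.2%, and PERMANOVA in 5.9%, 11.2% and 53.2%. At 50 v 25, with 15 in the tighter group and 10 in the looser, the rates are 95.8% and 24.6%; with 10 and 15 they are 0.0% and 6.1%. Equal mean proportions need not be equal centroids under this distance, so part of these rates may reflect location. The Euclidean results are the clean spread-only evidence. UniFrac was not simulated because no tree is available.

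**The case against.** Several objections limit the point.

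- **How much rests on ANOSIM.** A reader might infer that this one test decides the microbiota half of the primary outcome. The article does not say so. Composition is also approached through relative abundances, alpha diversity, ordination, redundancy analysis, ANCOM and LEfSe. Ordination plots would show a marked difference in spread, though only informally. ANOSIM remains the only method assigned to the between-group question for the whole community.
- **Covariates.** A reader might infer that the plan has no community-level method that can take BMI, diet or medication. Redundancy analysis can, and the exclusion criteria already restrict several medication effects. It is not given the role of the stage test.
- **The absent dispersion check.** An article may leave diagnostics and permutation schemes to a fuller plan, so their absence is not counted as an error. What stands is the stated choice of test.
- **Size.** No spread ratio appears in the article, and nothing there shows that disease groups are more heterogeneous than controls. At a ratio of 1.1 the inflation is slight. This objection stands in full as to magnitude.
- **Direction.** It is tempting to read the problem as false positives only. With a larger, more variable group ANOSIM almost never rejects, so loss of power is equally possible.
- **The alternative.** PERMANOVA also reacts to spread when groups are unequal or distances are non-Euclidean. This stands, and is why a dispersion test belongs beside it.

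The cluster-analysis label is loose, but the same sentence makes the purpose clear, so nothing turns on it.

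**Conclusion.** The point holds in this form: the named between-group test of whole-community composition confounds location with spread, so its p-value cannot carry a claim of compositional shift by itself. The mechanism is certain; the size is conditional. Under the assumptions stated above, rejection at 10 v 10 rises from about 5% to 18% and 61% as the SD ratio goes from 1 to 1.25 and 1.5. With the unequal sizes the plan allows, a ratio of 1.25 takes it to over 90% or about 0%, depending on which group is the more variable. PERMANOVA is clearly more robust in every case examined with unequal spread, but not immune. This is a worthwhile, inexpensive improvement to the analysis. It does not show that the study's conclusions would be wrong.

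**What to change.** In Data and statistical analysis:

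1. Make PERMANOVA, on the same Bray-Curtis and UniFrac distances, the between-group test of community composition.
2. Report PERMDISP beside every PERMANOVA, with group sizes. Where dispersion differs, interpret a significant PERMANOVA as location, spread or both, with particular caution if group sizes differ.
3. Where several sites per patient enter one test, restrict permutations to respect the patient: move whole patients for comparisons between stages, and permute within patient for comparisons between sites.
4. Keep the ANOSIM R statistic as description only.
5. Leave covariates mainly to the redundancy analysis already planned. A long covariate list is not advisable at 10 per group.

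The cost is revised wording and a little more analysis in standard software, with no new samples or data. Keeping group sizes close to equal would further protect the PERMANOVA result.
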